### Data analysis

Descriptive statistics will be compiled for all quantitative data collected. The interrupted time series (Study 1) will be analyzed using simulation modeling analysis [31], a trend analysis that provides good power to detect post-intervention trend changes when analyzing 30 time points or less per segment. As a precursor to modeling, the time series data will be plotted, analyzed visually for trends, and the degree of autocorrelation will be calculated. For Study 2, pre/post-changes on the clinician self-efficacy survey will be calculated using the paired *t* test, assuming the data are normally distributed or the signed rank test if not. Qualitative focus group data will be analyzed using directed content analysis [32], with initial codes based on questions derived from the focus group questions.

For Study 3, the non-randomized controlled trial of individual patients, between- and within-group differences on the outcome measures will be examined using repeated measures ANOVA.

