Through this project, we expect to see improved knowledge and practice change in inter-professional stroke rehabilitation teams, manifested as greater implementation of cognitive rehabilitation best practices and greater self-efficacy to do so. Following directly from positive practice change, we also expect to see improvements at the health system and health outcome levels. Individual rehabilitation professionals and teams as a whole will come to see themselves as having the specialized knowledge and skills to facilitate functional improvement in patients with cognitive impairments. With this, the number of patients with cognitive impairment who are accepted to inpatient rehabilitation will increase. Further, because previous research indicates that CO-OP is associated with improvements in functional independence, activity performance, self-efficacy, and participation, including in those with demonstrated cognitive impairment [10–15, 22, 23], we expect to see similar positive patient outcomes. Aligning with the three expected project outputs outlined previously in the manuscript, three specific research questions are posed:Is the implementation of CO-OP KT associated with a change in the proportion of patients with cognitive impairment following a stroke accepted to inpatient rehabilitation?Is the implementation of CO-OP KT associated with a change in rehabilitation clinicians’ practice, knowledge and self-efficacy related to implementing the CO-OP approach, immediately following and 1 year later?Is CO-OP KT associated with changes in activity, participation, and self-efficacy to perform daily activities in patients with cognitive impairment following stroke at discharge from inpatient rehabilitation and at 1-, 3-, and 6-month follow-ups?

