### Study 3: patient activity, participation, and self-efficacy outcomes

To answer question 3, a non-randomized study using historical controls will be conducted. We will compare a group of patients treated by stroke teams who have been exposed to the CO-OP KT intervention (intervention) to a group who have not been exposed (historical control). Prior to the implementation of CO-OP KT, control participants will be recruited, and after the CO-OP KT intervention, intervention participants will be recruited. During the 3-month period when the CO-OP KT intervention is being administered to teams and learning is being consolidated, no recruitment will occur. In addition to data elements universally collected for the ITS Study 1, Study 3 participants will undergo assessments to measure activity performance, participation, and self-efficacy.

Data collection points will occur at the individual patient participants’ admission to rehabilitation, discharge from rehabilitation, and at 1, 3, and 6 months following discharge. Follow-up assessments will be administered by telephone, a feasible and cost-effective alternative to face-to-face assessments [27]. Data will be collected by family member proxy if the patient participant is not capable of a telephone interview [28]. Table 1 provides a description of all outcomes, indicators, and timing of administration.

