### Recruitment and sample sizes

Five inpatient stroke rehabilitation units or combined stroke/neurology units in the TSNs have agreed to participate. Based on past experience, we estimate that the five units together will have approximately 80 admissions per month combined to contribute to the aggregate monthly data. For Study 1 (admission to rehabilitation), we will collect data from all patients aged 18 years or more who have completed inpatient rehabilitation with a primary diagnosis of stroke, defined as Rehabilitation Care Group (RCG) 01.1, 01.2, 01.3, 01.4 or 01.9. For Study 3, a subset of those patients will be recruited and the additional criteria of having at least some cognitive impairment will be applied, determined using the Montreal Cognitive Assessment© (MoCA©) [29]. The MoCA© is a 30-item test of cognitive impairment that includes elements of short-term memory recall; visuospatial capacity; aspects of executive functioning; attention, concentration, and working memory; language; and orientation. Patients with scores lower than 26 will be included. Additionally, patients will be required to have sufficient English language skills to complete the study assessments (see Table 1 for descriptions). Exclusion criteria are neurological diagnoses other than stroke, presence of major psychiatric illness or capacity issues requiring the use of a substitute decision maker under the Ontario substitute decision maker act. Based on data from a published acute rehabilitation CO-OP study [14], a sample size of 13 per group will have 80 % power to detect a between-group difference of 9 points on the FIM™, standard deviation of 8. Allowing for 30 % attrition from all sources, we will recruit 17 participants per group, 34 in total. Based on past projects, we expect a consent rate of one participant per site per month. Thus, recruitment is highly feasible, and will likely be completed in 4 months for each group.

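### Study 3: repeated measures ANOVA over five visits uses only participants with every visit, so later loss can also remove discharge data on COPM, SEG and SIS

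*Protocol article*

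**What the plan says.** The Data analysis section of the protocol article names one method for Study 3 and no other: "For Study 3, the non-randomized controlled trial of individual patients", "between- and within-group differences on the outcome measures will be examined using repeated measures ANOVA".

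The Study 3 section sets five data collection points: "admission to rehabilitation, discharge from rehabilitation, and at 1, 3, and 6 months following discharge". For the last three, "Follow-up assessments will be administered by telephone", with a family proxy when the patient is not capable of a telephone interview. Table 2 lists COPM, SEG and SIS as the Study 3 outcomes, plus the MoCA as a cognitive screening tool. It places FIM under Study 1, at admission and discharge and as change.

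Research question 3, at the end of the Background, asks about outcomes "at discharge from inpatient rehabilitation and at 1-, 3-, and 6-month follow-ups". Discharge is therefore of interest in its own right, alongside the later visits.

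Recruitment and sample sizes gives the numbers: 13 per group for 80 % power to detect 9 FIM points with SD 8, and then "Allowing for 30 % attrition from all sources, we will recruit 17 participants per group, 34 in total".

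**The concern.** Classical repeated measures ANOVA needs a complete set of visits for each participant. The plan combines that method with five visits, three of them by telephone up to 6 months after discharge, and with an expected loss of nearly a third of participants. Someone who is assessed at discharge but misses the 6-month call is left out of the whole analysis, including the discharge comparison for which the data were already collected.

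Two things are at stake. The first is precision, in a study of only 34 patients. The second is bias. If those who are lost differ in outcome from those who stay, the completers no longer represent the group, and recruiting extra patients does not correct that. Because the comparison uses historical controls, retention could also differ between the two recruitment periods.

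**Working it through.** **Inputs from the protocol.** 17 recruited per group; 30 % attrition from all sources; five visits; difference 9 and SD 8 on the FIM. Alpha is not stated; two-sided 0.05 is assumed.

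**The plan's own figure.** n per group = 2 × (1.96 + 0.84)² × 8² / 9² = 15.68 × 0.790 = 12.4, rounded up to 13. This reproduces. Power at 13 per group is 82 % by the normal approximation and 79 % by the noncentral t, both close to the stated 80 %. The 17 is 13 × 1.3 = 16.9; division would give 13 / 0.7 = 18.6, so 19.

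**Completers.** 17 × 0.7 = 11.9, about 12 per group, or 24 of 34. This is below the 13 that the calculation aims for.

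**What listwise exclusion does.** Take 34 participants, 10 of whom lack only the 6-month visit. Records collected: 34 × 5 − 10 = 160. Records used: 24 × 5 = 120. Of the 40 collected records left out, 10 are discharge assessments. A standard repeated measures ANOVA routine (AnovaRM in statsmodels) refused simulated data of this pattern as unbalanced and ran only on completers.

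**Discharge records left out, by timing of loss.** Total loss is held at 30 %. Power is for 9 points, SD 8, by the noncentral t with 2n − 2 degrees of freedom and noncentrality 9 / (8 × √(2/n)).

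| Loss before discharge | Seen at discharge, per group | Left out (seen − 11.9) | Power, all seen at discharge | Power, completers only |
|---|---|---|---|---|
| 0 % | 17 | 5.1 | 89 % | 75 % |
| 10 % | 15.3 | 3.4 | 85 % | 75 % |
| 15 % | 14.4 | 2.6 | 83 % | 75 % |
| 30 % | 11.9 | 0 | 75 % | 75 % |

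In the first row the standard error ratio is √(12/17) = 0.84, so using everyone seen at discharge narrows the standard error by up to 16 %. The power columns use the FIM difference because the protocol gives no difference or SD for COPM, SEG or SIS. They show the scale of the loss and are not the power of any five-visit outcome.

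**Bias illustration.** Assumed inputs, none of them in the protocol: about 30 % loss overall; true difference 9 / 8 = 1.125 SD at each visit; correlation 0.6 between discharge and 6-month scores; dropout after discharge more likely with a lower discharge score, on the logit scale, in both groups. Large-sample simulation of the completers gives:

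| Log-odds of dropout per SD | Shrinkage at discharge | Shrinkage at 6 months |
|---|---|---|
| 0.25 | about 1 % | about 1 % |
| 0.5 | about 5 % | about 3 % |
| 1 | about 13 % | about 8 % |

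In the same set-up at log-odds 1, a regression of 6-month on discharge scores that uses everyone seen at discharge recovers 1.13 SD at 6 months. This stands in for a likelihood-based model and shows that such a model removes this bias when loss depends only on observed scores.

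**The case against.** - **The article does not state a completers-only rule.** It does not say that one model spans all five visits, that incomplete participants are excluded or that nothing is imputed. A statistical analysis plan that is not shown could settle this. That stands as a limit on certainty. The point nevertheless concerns the method the article names, and exclusion follows from that method in its classical form.
- **A reader might infer that power at discharge falls from 89 % to 75 %.** The documents do not support this. Those figures rest on the FIM, which has no 1-, 3- or 6-month value, so a missed 6-month call removes no FIM data.
- **A reader might take 5 of 17 per group as the expected loss of discharge data.** It is the upper end. The 30 % covers all sources with no timing, and loss before discharge leaves out no discharge record.
- **The bias depends on assumptions.** The protocol gives no dropout mechanism. Proxy assessment partly protects against function-related loss, although it does not cover death, withdrawal or loss of contact. With weak dependence the bias is negligible.
- **The attrition allowance already covers lost numbers.** In part it does, but 11.9 completers fall short of 13, and added recruitment does not address selection.
- **Sphericity.** It might be raised as a further flaw. It affects the within-subject tests, standard corrections exist, and an article need not name them. No weight is placed on it here.

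**Conclusion.** The concern holds in a limited form. For COPM, SEG and SIS, the named analysis in its classical five-visit form makes poor use of the follow-up that the plan expects to obtain. It leaves out 0 to about 5 of 17 observed discharge assessments per group, and it relies on loss being unrelated to outcome. Possible shrinkage of the discharge difference runs from about 1 % to about 13 % over the assumed range of dropout dependence; the protocol supplies nothing to narrow that range. The FIM comparison at discharge is not affected by missed telephone visits. The change is worth making before recruitment starts because it is nearly free, but the documents do not show that the planned result would be materially wrong. Nor do they rank discharge above the later visits, so there is no ground for treating it as the lead time point.

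**What to change.** In the Data analysis section, replace repeated measures ANOVA for Study 3 with a likelihood-based linear mixed model for repeated measures that uses all available visits. Specify categorical time, group, group-by-time and Kenward-Roger degrees of freedom. Start from an unstructured covariance and name in advance a simpler structure to use if the model does not converge: five visits need 5 × 6 / 2 = 15 covariance parameters, and there are at most 34 patients. Report the group contrast with its 95 % CI at discharge and at 1, 3 and 6 months, without ranking one above the others.

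The cost is a change of wording. Standard software suffices, no patient or visit is added, and the trial status is not yet recruiting. The model relies on data being missing at random, a weaker condition than the ANOVA needs but still an assumption, and the covariance may have to be simplified. It does not deal with confounding from the use of historical controls, which is a separate matter.

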**Table 2 Tab2:** Outcomes, indicators, and timing for all studies

Outcomes	Indicators and description	Timing
Study 1: health system: data obtained from electronic referral system, health record, and NRS		
Access to inpatient rehabilitation	Monthly totals: # of inpatient rehab referrals, # of admissions, # declined; reasons for declined referrals	• −T28 to −T1 • T1 to T15
Inpatient rehab outcomes	Average monthly functional independence measure (FIM™) motor and cognitive scores (admission, discharge, and change)	• −T28 to −T1 • T1 to T15
	Monthly frequency of discharge locations (home, home with services, assisted living facility, or acute care)	
Study 2: health knowledge: data obtained from stroke rehabilitation team members and chart audits		
Rehabilitation team member practice change	Chart audits will be conducted 6 months (+/−1 month) before CO-OP KT implementation as a baseline and to confirm practice gaps previously identified with interviews [4], and repeated at 6 and 12 months (+/−1 month) following the CO-OP KT intervention. The chart audit review criteria will center around documentation of functional goals (e.g., independence with upper body dressing), rather than impairment-reduction goals (e.g., increase arm strength); evidence of patient involvement in the goal-setting process; evidence of teaching of cognitive and problem-solving strategies as an intervention technique; evidence of use of guided discovery as an intervention technique	• −T6 • T6, T12
Stroke rehab professional self-efficacy with knowledge and skills related to CO-OP	CO-OP essential elements self-efficacy tool: participants are asked to rate their ability to perform 25 elements on a 10-point scale, with 1 indicating that they cannot perform the element at all and 10 indicating that their performance is excellent. Face validity evaluated by five members of the International CO-OP Academy	• −T1 • T1 • T12

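### Study 3's 80 % power is not tied to any term of its repeated measures ANOVA, and the group main effect of that model would dilute the effect by averaging in the admission visit

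*Protocol article*

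**What the plan says.** The sample-size paragraph (Recruitment and sample sizes) states that "a sample size of 13 per group will have 80 % power to detect" its target effect. The paragraph specifies that effect as follows: "between-group difference of 9 points on the FIM™, standard deviation of 8". After an allowance for attrition, "we will recruit 17 participants per group, 34 in total". It names no test, significance level, time point or correlation, and does not say whether the SD is that of a score or of a change.

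The Data analysis section gives one sentence for Study 3: "between- and within-group differences on the outcome measures will be examined using repeated measures ANOVA". It names no treatment term and does not say how the admission value enters.

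The Study 3 section fixes the visits: "Data collection points will occur at the individual patient participants’ admission to rehabilitation, discharge from rehabilitation, and at 1, 3, and 6 months following discharge". It also says that the Study 1 data elements are available for Study 3 patients. That is how the FIM reaches Study 3. Table 2 lists it for Study 1 as "Average monthly functional independence measure (FIM™) motor and cognitive scores (admission, discharge, and change", that is, at two occasions. COPM, the self-efficacy gauge (SEG) and the Stroke Impact Scale (SIS) are the Study 3 outcomes with five visits in Table 2.

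**The concern.** In a repeated measures ANOVA with visit as the repeated factor, the between-group term compares each patient's average over all visits. The admission value is taken before the rehabilitation stay, so it cannot carry an effect of the treatment given during that stay. Averaging it in shrinks the estimated effect, and the shrinkage is greatest for the FIM, where admission is one of only two visits. The FIM is also the measure on which Study 3 was sized.

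Two things are at stake. One is power: the 80 % belongs to a comparison of one value per patient and does not carry over to the group main effect. The other is bias: Study 3 uses non-randomized historical controls, and the project itself expects more patients with cognitive impairment to be admitted after the intervention. The groups may therefore differ at admission, and the main effect takes in any such difference in full.

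**Working it through.** **Inputs from the protocol article.** 13 evaluable per group, difference 9, SD 8; 17 per group recruited; FIM at admission and discharge; five visits for COPM, SEG and SIS.

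**Assumptions (not stated in the document).** Two-sided 5 % level; SD 8 at each visit unless noted; no admission difference; effect of 9 at discharge; within-patient correlation ρ from 0.3 to 0.9.

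**Step 1: reproduce the stated figure.** Normal formula: n = 2 × [8 × (1.960 + 0.842) / 9]² = 12.4, rounded up to 13 per group. At n = 13 the power is 81.8 % by the normal formula and 78.6 % by the noncentral t. A one-sided 5 % test would need only 10. The plan's figure is thus a two-sided two-sample comparison of one value per patient.

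**Step 2: terms available with two FIM visits, 13 per group.** All use the noncentral t.

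- Group main effect: difference (0 + 9)/2 = 4.5; SD of a patient's mean = 8√((1+ρ)/2).
- Group-by-time: difference 9; SD of change = 8√(2(1−ρ)).
- Discharge adjusted for admission: difference 9; residual SD = 8√(1−ρ²). This is approximate, because the one degree of freedom for the covariate is ignored.

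| ρ | Main effect: SD, power | Group-by-time: SD, power | Adjusted discharge: SD, power |
|---|---|---|---|
| 0.3 | 6.45, 40 % | 9.47, 64 % | 7.63, 82 % |
| 0.5 | 6.93, 36 % | 8.00, 79 % | 6.93, 89 % |
| 0.7 | 7.38, 32 % | 6.20, 94 % | 5.71, 97 % |
| 0.9 | 7.80, 29 % | 3.58, over 99 % | 3.49, over 99 % |

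Simulation of the first two terms at ρ = 0.3, 0.5 and 0.7 agreed (main effect 40 %, 35 %, 32 %; group-by-time 65 %, 78 %, 94 %). With all 17 per group retained, the main effect has about 51 % at ρ = 0.3 and 37 % at ρ = 0.9.

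**Step 3: if SD 8 is the SD of change.** With two visits the group-by-time test is a two-sample t test on change, so its power is 78.6 %, close to the stated 80 %.

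**Step 4: a five-visit outcome with the same standardised effect held at all four later visits.** The main effect estimates 4/5 of the effect (7.2 in place of 9) with SD 8√((1+4ρ)/5). Power is 91 %, 81 %, 71 % and 63 % at ρ = 0.3, 0.5, 0.7 and 0.9.

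**Step 5: admission imbalance, as an illustration.** Suppose the intervention group starts a points lower and gains 9 points more.

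- Main effect on two visits: (−a + 9 − a)/2 = 4.5 − a, which is zero at a = 4.5.
- Change from admission: 9.
- Adjusted discharge comparison, with slope ρ: 9 − a(1−ρ). At a = 4.5 and ρ = 0.5 this is 9 − 2.25 = 6.75.

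The last two agree when a = 0 and differ otherwise.

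**The case against.** A reader might infer that Study 3 as planned has 30 to 40 % power and not 80 %. The document does not support that. The Data analysis section does not make the group main effect the treatment test. Research question 3 asks about changes at discharge and later visits, which points to the group-by-time term or to contrasts at each visit. The SD of 8 may be that of a change score, in which case 13 per group is close to the right size for the two-visit group-by-time test. Halving of the effect applies only to the two-visit FIM, and the outcomes that Table 2 lists for Study 3 have five visits. All of this stands, and it limits the low figure to one reading of one measure.

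It can also be said that the test term, the handling of baseline and the assumed correlation are details that a condensed article leaves to the full plan. Silence on them alone would not be a finding. But the article does state a power and does name a model, and the most literal reading of a between-group difference in that model is the main effect, to which the stated power does not apply. Using admission as an outcome level in that test is a weak choice, not just an unstated one.

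Finally, adjusting for the admission value is not neutral when controls are historical. With groups that differ at admission, the adjusted comparison and the comparison of change estimate different quantities, and neither is right by default. This stands too, and is why both should be reported.

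**Conclusion.** The point holds in a conditional form. The 80 % reproduces as a comparison of one value per patient and is not attached to any term of the named model. Read from the group main effect on the FIM, the 9-point effect becomes 4.5 points and power is about 40 % to 29 % for correlations 0.3 to 0.9. That range rests on two visits, SD 8 per visit, equal groups at admission, 13 per group and a two-sided 5 % level. Read from the group-by-time term, power is 64 % to 94 % for correlations 0.3 to 0.7, or 78.6 % if SD 8 is that of change. For a sustained five-visit effect the loss in the main effect is one fifth of the effect, not half. So the power for the sized effect runs from about 30 % to over 90 %, depending on a choice that the document leaves open. Nor would it follow that any null result in Study 3 is an artefact: that would require the main effect to be the test actually used.

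**What to change.** In Data analysis, state that admission is not an outcome level in the between-group test. Make the Study 3 treatment test the group difference at discharge adjusted for the admission value, with the same adjusted comparison at discharge and at 1, 3 and 6 months for COPM, SEG and SIS. Report the group-by-time contrast (change from admission) as a sensitivity analysis. Say that the two can differ if the groups differ at admission, and that neither removes all confounding with historical controls.

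In Recruitment and sample sizes, state that the 80 % refers to the discharge comparison, whether SD 8 is that of the score or of change, and the range of correlations assumed.

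The cost is a few sentences, one degree of freedom and one extra analysis. Admission values are already collected, and no more patients are needed for this change.

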## Background

Patients with cognitive impairments following a stroke are often denied access to inpatient rehabilitation [1], despite evidence of its benefits for them [2]. These patients comprise up to 30 % of stroke patients [3]. In the instances when they are admitted to inpatient stroke rehabilitation, they generally receive services based on outdated impairment-reduction models, rather than recommended function-based approaches [4]. These two issues, reduced access to rehabilitation and the knowledge-to-practice gap, both stem from a reported lack of skills and knowledge on the part of stroke rehabilitation teams [4]. To address these issues, we will implement and evaluate a multi-faceted, supported, integrated knowledge translation (KT) initiative, targeted specifically at the inter-professional application of the cognitive orientation to daily occupational performance (CO-OP) approach [5]. The CO-OP approach is a contemporary, effective, cognitive strategy-based treatment approach aligned with Canadian stroke best practice recommendations for cognitive rehabilitation [6]. The long-term objective of this knowledge translation initiative is to optimize functional outcomes for individuals with cognitive impairments following a stroke. Three outputs are expected: (1) increased proportion of patients with cognitive impairments admitted to inpatient stroke rehabilitation; (2) enhanced capacity of inter-professional stroke rehabilitation team members to implement a cognitive-strategy based treatment approach; and (3) improved immediate and long-term functional outcomes for patients with cognitive impairments discharged from inpatient stroke rehabilitation.

This project is a collaboration between a group of knowledge users, lead by [name], and a group of researchers, lead by [name]. Lead knowledge user and decision maker, [name], is one of three regional directors within the Toronto Stroke Networks (TSNs), an organization charged with overseeing service delivery is in line with best practices and optimization of resources [7]. [name] has convened a knowledge user team of educators, a community re-engagement specialist, and management collaborators. To ensure an integrative KT strategy, these partners have been involved with every aspect of this project’s design, beginning with pre-project work to identify the problem and develop plans to address it.

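### Study 3 compares patients admitted before and after an intervention meant to change who is admitted, and the only analysis named, a repeated measures ANOVA, does not adjust for admission severity

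*Protocol article*

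**What the plan says.** All references are to the Protocol article.

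- **Design** (Study 3 section): "a non-randomized study using historical controls will be conducted". On timing: "Prior to the implementation of CO-OP KT, control participants will be recruited, and after the CO-OP KT intervention, intervention participants will be recruited". Group therefore coincides completely with admission period.
- **Expected change in admissions** (Background): the first expected output is "increased proportion of patients with cognitive impairments admitted to inpatient stroke rehabilitation". Later in the Background the expectation is repeated: "the number of patients with cognitive impairment who are accepted to inpatient rehabilitation will increase".
- **Prognosis** (Background): patients with cognitive impairment are described as having worse outcomes, including more dependency and disability.
- **Eligibility** (Recruitment and sample sizes): Study 3 patients are a subset of the Study 1 admissions. They must have a MoCA score below 26, with no lower limit. Patients who need a substitute decision maker are excluded, and enough English for the assessments is required.
- **Analysis** (Data analysis): "between- and within-group differences on the outcome measures will be examined using repeated measures ANOVA". The text calls the comparison non-randomized but names no covariate, matching, weighting or stratification.
- **Handling of outside changes** (Potential challenges and their solutions): discussed for the time series only, not for Study 3.
- **Data available** (Study 3 section): "In addition to data elements universally collected for the ITS Study 1, Study 3 participants will undergo assessments". The Study 1 elements include age, sex and FIM total, motor and cognitive scores. Table 2 adds COPM, SEG, SIS and MoCA, with admission as the first assessment point.

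**The concern.** The project's first aim changes the population on which its third aim is measured. If the units begin to accept patients they would previously have declined, the post-implementation sample may be more severely affected at admission than the historical controls, even though both groups meet the same MoCA threshold. The named ANOVA cannot separate that difference from an effect of CO-OP KT.

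Having admission as one of the repeated measurements helps only in part. The group-by-time term removes a constant difference in level. It does not remove regression to the mean or a different recovery rate in more impaired patients. The between-group term, which the analysis sentence also covers, carries the level difference directly. A Study 3 result in either direction could then partly reflect case mix.

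**Working it through.** **1. The plan's own figure.** Inputs from Recruitment and sample sizes: difference 9 FIM points, SD 8, power 80 %. Two-sided 5 % is assumed, as the article does not state it. By the normal approximation, n per group = 2 × (1.960 + 0.842)² × 8² / 9² = 12.4, rounded up to 13. The stated 13 is reproduced. Exact two-sample t-test power at 13 per group is 78.6 %. With 17 recruited and 30 % lost, 17 × 0.70 = 11.9, about 12 per group remain, and t-test power is 75 %. The calculation has no allowance for confounding.

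**2. Bias from a severity shift.** Assumptions, not in the protocol: the post-implementation group is lower at admission by s = 0.25 to 0.5 SD, the correlation between admission and follow-up is r = 0.6, the SD is 8 at both occasions, and there is no true effect.

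| Contrast | Formula | s = 0.25 | s = 0.5 |
|---|---|---|---|
| Follow-up difference | −s × r × SD | −0.25 × 0.6 × 8 = −1.2 | −0.5 × 0.6 × 8 = −2.4 |
| Change (group-by-time) | +s × (1 − r) × SD | +0.25 × 0.4 × 8 = +0.8 | +0.5 × 0.4 × 8 = +1.6 |

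As a share of the planned 9 points, these are 13 % to 27 % against CO-OP KT for the follow-up difference, and 9 % to 18 % in its favour for the change contrast. The change figure reflects regression to the mean only. Slower recovery in more impaired patients would push the other way.

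**3. Effect on power for the follow-up difference.** At 12 per group the apparent effect falls from 9 to 9 − 1.2 = 7.8 or 9 − 2.4 = 6.6 points. t-test power falls from 75 % to 63 % or 49 %.

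**4. False-positive rate with no true effect.** Simulation at 13 per group with a 4-point shift (0.5 SD) and correlation 0.5 to 0.7:

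| Analysis | Rejection rate (nominal 5 %) |
|---|---|
| Follow-up difference | 9 % to 14 % |
| Group main effect (mean of admission and follow-up) | 18 % to 20 % |
| Change | 8 % to 10 % |
| Adjusted for the admission score | about 5 % |

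**5. What adjustment does to power.** Simulation at 12 per group, true effect 9 points, one covariate with correlation 0.5 to 0.6, shift 0 to 0.5 SD:

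- one admission covariate: about 82 % to 89 %;
- two covariates, the second adding nothing: about 81 % to 88 %;
- admission outcome, MoCA, FIM motor, age and unit (4 + 4 = 8 parameters for 24 patients), with the extra ones adding nothing: about 63 % to 72 %, below the 75 % of the unadjusted test.

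The simple formula that divides the standardised effect 9/8 = 1.125 by √(1 − r²) gives 86 % to 91 %. It charges nothing for lost degrees of freedom or baseline imbalance, so it does not describe a long covariate list.

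**The case against.** The strongest case on the other side has five parts.

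*The article does not say the ANOVA is unadjusted.* It is a condensed text, and covariates are often left to an analysis plan. This stands as a caveat: the absence of adjustment is inferred from one sentence. But that sentence fixes a method for a comparison it calls non-randomized, and the project's own hypothesis creates the confounding, so the point is about the choice made and not merely about missing detail.

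*A shift is not guaranteed.* A reader might infer that the intervention group must be more impaired if Study 1 succeeds. The documents do not support that. Both groups are limited to MoCA below 26, and patients who need a substitute decision maker are excluded. More patients below the threshold does not by itself mean lower scores among them. Consent also shapes the sample: about one participant per site per month is expected, against about 80 admissions a month across the five units. This objection stands in full.

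*The direction is open.* A reader might infer that the bias runs mainly against CO-OP KT and would make a null result uninterpretable. The change contrast is biased the other way under the same assumptions, and a bias of 1 to 2 points in 9 does not make a result uninterpretable. This also stands.

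*The size rests on assumed inputs.* Neither the shift nor the correlation is in the protocol. FIM is the sample-size basis, while Table 2 lists COPM, SEG, SIS and MoCA for Study 3; the correlation may differ for those, COPM especially, since it rates self-selected activities. The figures are illustrations.

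*The design is openly observational.* The research question asks about association, and adjustment cannot remove secular or unmeasured differences. True, but that is no reason to leave measured severity out of the model.

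**Conclusion.** The concern holds in a limited form. The protocol expects CO-OP KT to change admissions, says the patients concerned do worse, samples Study 3 on either side of that change, and names an analysis with no adjustment. A severity shift is plausible and would be confounded with the patient effect.

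Under the stated assumptions the distortion is moderate, and its sign changes with the contrast, so both a favourable and an unfavourable result would be open to a case-mix explanation. This should be fixed before recruitment, but it does not invalidate Study 3.

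**What to change.** - **Primary Study 3 analysis:** a repeated-measures model of the post-admission outcomes on group, time and group-by-time, adjusted for the admission value of the outcome and admission MoCA only. With about 12 to 17 patients per group, the list should go no further.
- **Supportive:** keep the unadjusted repeated measures ANOVA, labelled as such.
- **Sensitivity:** add FIM motor score, age or unit only in separate analyses, and claim no power of 86 % to 91 % for a long list.
- **Reporting:** show admission MoCA, FIM, age and unit by group, so that any shift is visible.
- **Interpretation:** state that adjustment removes measured case mix only, not secular or unmeasured differences, and that conclusions remain associations.

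**Cost:** analysis wording and one or two degrees of freedom. The data are already to be collected, and the article gives the trial status as not yet recruiting, so the model can be fixed before any Study 3 data are seen.
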